#### Guiding frameworks

We have adopted three frameworks to guide our study. Versions of them have been used by different research studies in the field of knowledge translation and implementation science. Phase 1 of the study will be framed by a knowledge transfer, dissemination, and utilization in organizations conceptual framework (see Fig. 1). The framework and its matching logic model (see Fig. 2) will drive the evaluation of the effectiveness of the individual workplace implementations. This framework was developed specifically for workplace-based occupational health and safety initiatives [70, 71] by one of this project’s team members (DK) and has recently been used by Allen et al. [72]. The model’s five variables focus on the outer context, the knowledge source and characteristics, the workplace context, the facilitation of the knowledge transfer, indicators of knowledge exchange, and stages of knowledge utilization. The indicators of the latter will be conceptual, effort to use, procedural, and structural use. The short-, medium-, and long-term outcomes focus on the workplaces’ structural, policy, and educational changes.

**Fig. 1 Fig1:**
[figure not shown]
Sun Safety at Work phase I conceptual framework

**Fig. 2 Fig2:**
[figure not shown]
Sun Safety at Work phase I logic model

Phase 2 of the study will be framed by a dissemination and knowledge transfer framework (see Fig. 3) and its matching logic model (see Fig. 4). The evidence-based knowledge that drives this dissemination model will be informed by the findings from phase 1. This framework is an adaptation of Harris et al.’s [73] and emphasizes the relationship between researchers, disseminating organizations, and user organizations for successful knowledge exchange [73]. The user organizations for this project will include workplaces, industry and not-for-profit decision-makers and organizations, and policy advocates. The setting of the knowledge dissemination will include modifiable variables such as relationships and networks, workplace policies, and funding allocations, and will take into account unmodifiable factors such as the economic and political climate. This framework incorporates principles of social marketing in the dissemination approach and intensive and integrated knowledge transfer strategies, which align closely with the objectives of phase 2.

**Fig 3 Fig3:**
[figure not shown]
Sun Safety at Work phase II conceptual framework

**Fig. 4 Fig4:**
[figure not shown]
Sun Safety at Work phase II logic model

In the experience of the researchers, a determination of readiness to change is essential particularly for phase 1 of the study since it is a major driver of the success of any workplace-based intervention [74]. Hence, an organizational readiness for change “Sun” model (see Fig. 5) was used especially for the recruitment of workplaces. It was used as a communication tool by the study partners to help explain the project to potential workplaces. The model is based on the transtheoretical model [75] and an adaptation of Shea et al.’s ”Determinants and outcomes of organizational readiness for change” model [76]. The model takes into account workplaces’ perception that change (on sun and heat protection) is needed, important, worthwhile, or beneficial, and their self-appraisal that they have the needed resources to make the changes [77]. We conceptualize workplaces to be at one of five possible stages of readiness to implement sun safety interventions for outdoor workers: (1) pre-contemplation: occupational health and safety (OHS) is not on the organization’s radar; (2) contemplation: OHS is on the organizational members’ radar; (3) preparation: the organization is engaged in OHS; (4) action: sun safety is on the organization’s radar; and, (5) engaged: the organization is already engaged in sun safety practices. In our workplace recruitment, workplaces have self-identified where they believe they fit on the continuum.

**Fig. 5 Fig5:**
[figure not shown]
Sun Safety at Work organizational readiness for change model

We will also create an evaluation framework in order to compare the 13 case studies. The cases will be compared on industry, size of workplace, readiness to change, the interventions they choose, the barriers and facilitators, and changes the three-points-in-time evaluation. The major outcomes for the evaluation are the changes in policy, procedures, and practices at the workplace level.

#### Phase 1: workplace-based sun-safety intervention

The aim of phase 1 is to expand upon the success of existing sun-protection programs by leveraging their findings into the development of a nationally-applicable Canadian-based workplace sun safety program. In this first phase of the study, we will recruit 13 workplaces across four Canadian provinces (i.e., British Columbia, Ontario, Nova Scotia, and New Brunswick) and conduct intensive implementations with the help of Sun Safety Advisors in the role of knowledge brokers. We will work with these workplaces over a period of approximately 18 months.

#### Sampling and recruitment of workplaces

The study is focusing on workers employed with utilities such as electrical distribution companies and those employed with medium-to-large municipalities and provincial wilderness parks. The initial criterion will be whether the organization has (at least) 20–100 employees engaged in outside work. Such outside work will be primarily of a brush-clearing, grounds-keeping, or landscaping nature (i.e., employees undertaking outdoor work on “soft” surfaces). It is anticipated that many utilities will have employees engaged in clearing vegetation from right-of-ways and trimming trees and shrubs near power lines. Municipalities will have employees maintaining municipal properties such as parks and will be engaged in grounds-keeping, lawn-mowing, and landscaping. It is anticipated that some organizations will contract out such brush-clearing or landscaping work and so will not be suitable participants. It is also anticipated that most OHS professionals will have to gain the support or permission of others in the organization in order to participate.

Workplaces were recruited through convenience sampling by using existing contacts of project partners and supporters. A number of the supporters who wrote letters of support for the project are workplaces who are interested in participating in the project; these were contacted through local and regional contacts of the partners on the project. Other potential participants were selected using a database of approximately 10,000 OHS professionals; individuals who occupy the position of OHS “manager,” “coordinator,” “advisor,” “lead”, and so on (there is great diversity of job titles for the individuals who oversee an organization’s OHS efforts). Initial contact was made with the OHS professional employed by a municipality, wilderness park, or utility by senior partners on the study to determine the personal interest of the OHS professional in the aims of the project and to ascertain the numbers and nature of work of the outside workers.

Once this initial contact with the OHS professional had been made, a senior partner on the study attended a group meeting, organized by the OHS professional, of the senior management, operational supervisors, and union representatives. Questions were answered on the purpose of the study, the benefit to the company, the resources that the company will need to dedicate to the project, and how information will be distributed back to management and workers. In general, a letter of voluntary commitment and involvement between the company and the research team completed the recruitment process. However, to ensure that the initial engagement process was respectful to the workplace and to establish a good relationship from the start, the project team worked with each workplace to assist them in gaining the necessary internal approval to participate. As such, whatever form of correspondence for approval was appropriate for each workplace was supported, i.e., we did not use a one-size-fits-all model for gaining workplace sign-on/approval to participate.

At the first meeting with the workplaces, they were shown a number of communication pieces on the study, such as an invitation letter, the organizational readiness for change “Sun” model (see Fig. 5), a flyer on the study (see Fig. 6), and an overview diagram of the project (see Fig. 7). These pieces have proved to be very useful to open up the discussion with management and organized labor (if the company is unionized) on their values and beliefs about health and safety in general and sun protection in particular.

**Fig. 6 Fig6:**
[figure not shown]
Sun Safety at Work informational flyer for workplaces

**Fig. 7 Fig7:**
[figure not shown]
Sun Safety at Work project overview

#### Recruitment of Sun Safety Advisors

An ongoing positive relationship with the workplaces will be critical to the success of the project. To this end, a project coordinator was hired, and then local project officers (the Sun Safety Advisors) were hired in each province to act as knowledge brokers to build upon this initial recruitment of the workplaces (see Fig. 8 for the interview guide and Fig. 9 for the screening tool that was used during the hiring process). The advisors were selected for their strong background in occupational health and safety, public health, and work with workplaces. They received an initial training in the first quarter of the year to ensure they were all starting with a basic knowledge of the importance of sun and heat protection (see Fig. 10 for the agenda of the training session). The importance of the role of the knowledge broker has been well-explored in the KT literature [78, 79].

**Fig. 8 Fig8:**
[figure not shown]
Sun Safety Advisor—interview guide

**Fig. 9 Fig9:**
[figure not shown]
Sun Safety Advisor screening criteria for hiring

**Fig. 10 Fig10:**
[figure not shown]
Sun Safety at Work sun safety advisor training meeting

The Sun Safety Advisors will interact with one to four workplaces each depending upon geographical convenience. To initiate their relationship with the workplaces, they will meet with their worksites together with the project partner who made the initial contact to reassure the workplace of the level of support offered by the project team. They will engage with the participating worksites (including regular face-to-face contact) with management and workers, and will identify an internal “workplace champion” with whom to work closely. The workplace champion will be the workplace liaison and local project sponsor. The importance of the champion role has also been well explored as a means to ensure sustainability [80]. In previous projects of this type, the workplace occupational health and safety professional has often fulfilled this “workplace champion” role because of their involvement in occupational health and safety projects.

The project officers will collect the evaluation data at base-line before and after the first summer. This includes worker surveys and a face-to-face interview with the health and safety champion and managers. The interview information will focus on assessing the workplace’s organizational readiness for change; the worker surveys will evaluate workers’ awareness and knowledge of heat and sun protective behavior and practices, and when compared with the second evaluation, we will have metrics of change due to the intervention.

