### Occupational sun safety measures

The World Health Organization recommends that sun protection be provided once the UV index exceeds 3 [15]. For Canada, this means UV protection should be used between April and August in many locations (e.g., in Edmonton), with this extending from March through October in some locations (e.g., in Toronto) [16]. For outdoor workers, general protection measures include the following: engineering controls (for example, the provision of shade, window tinting); administrative controls (educational programs, recognition of individual susceptibilities, sun avoidance strategies, and scheduling of work hours outside of peak UV times); and personal protective equipment (PPE) (wide-brimmed hats, long-sleeved shirts and long pants, use of sunscreen, and eye protection) [17]. These measures should be part of a broader risk management approach that also includes implementing workplace policies and a risk management process [18].

Despite the wide-spread availability of educational materials and sun safety resources (for example, the Canadian Dermatology Association’s Sun Safety for Outdoor Workers Manual or *Be Sunsible*www.besunsible.ca and other resources [19–21]) and the easy availability of a wide range of protection measures, numerous studies have shown that implementing effective sun protection programs for outdoor workers continues to be highly challenging. Few workers are considered to be adequately protected (in some cases 10 % or less) [10, 22–28] with the face and lower arms being the least protected sites [24, 29] and the use of sun screen and wide brimmed hats particularly low [23, 25–27, 30–32]. As such, improving sun protection among outdoors workers is a strategic objective under the Canadian Strategy for Cancer Control [33] and is a key recommendation from the Second National Sun Survey [34].

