#### Two-phased intervention design

The project takes an integrated knowledge translation (IKT) approach that brings together researchers, policy advocates, and practitioners throughout the research process. The partners are Ryerson University’s School of Occupational and Public Health, the Occupational Cancer Research Centre, Sun Safe Nova Scotia, the Occupational Health Nurses Association Nova Scotia, CAREX Canada, Canadian Cancer Society Nova Scotia, Centre for Research Expertise in Occupational Disease, and Alberta Health Services. The study partners have been involved and engaged in the initial conception of the study, the recruitment of workplaces and Sun Safety Advisor knowledge brokers, the creation of the sun safety program suite of resources for workplaces, determining the data that will be collected at three points in time during the study, and the dissemination phases of the study. The partners are based in the four Canadian provinces (Ontario, Nova Scotia, New Brunswick, and British Columbia) in which the interventions will take place and local partners will take the lead in supervising the local interventions.

The research team is interdisciplinary in nature, with researchers from epidemiology, occupational health and safety, occupational medicine, law, sociology, knowledge translation, and adult education. The study uses a mixed methods approach, with the qualitative data analysis being used to help inform and gain a better understanding of the quantitative findings [69]. The project has two complementary phases of activities, in which phase 2 builds on the outcomes of phase 1. Phase 1 is characterized by the intensive engagements with 13 workplaces across Canada and a three-phased evaluation: before the implementation, after the first summer, and 18 months after the project starts (including a second summer). Phase 2 includes an extensive outreach to industry and not-for-profit decision-makers and organizations who are interested in sun protection and policy-level discussions with industry decision-makers, and the creation of a website with tailored resources for workplaces. The process and impact evaluations will be driven by conceptual frameworks to ensure that the phases are theoretically linked and to help us to understand the knowledge translation needs and requirements in rolling out a sun and heat protection programs and policies in workplaces across Canada.

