#### Phase 1: data collection and analysis

The evaluation will employ a multiple case study approach [81], with the participating workplaces as the units of analysis. The evaluation of the cases will be guided by the conceptual framework for knowledge transfer, dissemination, and utilization for sun safety in outdoor workplaces (Fig. 1) to capture changes in programs, policies, and procedures. Workplace evaluations will occur at three points in time. The baseline assessment will focus on understanding the unique characteristics of each workplace, their occupational health and safety management system, and their current sun safety policy and practices. The second evaluation will be conducted after the first summer (mid-point of the study). The third workplace evaluation will be conducted 18 months after the study’s start date. Finally, a cross-case evaluation matrix will be used to determine generalizable patterns and themes.

Data collection will use mixed methods involving multiple sources of information including semi-structured key informant interviews and focus groups with workers, management, and the occupational health and safety specialist to determine the current occupational health and safety policies and procedure, readiness to change, organizational culture, and barriers/facilitators to sun safety programming (for example, see Fig. 11 information and consent form). The focus groups with employees will explore barriers and facilitators from the perspective of the different workplace parties—workers, supervisors, managers, and occupational health and safety specialists—and a survey will address individual knowledge, attitudes, and behaviors toward sun safety in the workplace. Site observations will record the use of sun safety practices, and a UV dosimetry assessment will measure UV exposure of the employees in the second summer of engagement.

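### The change in worker practice from baseline to the second evaluation mixes season with program, so it cannot be read as change caused by the program

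*Protocol article*

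**What the plan says.** The protocol article fixes three evaluations. Under Two-phased intervention design they fall "before the implementation, after the first summer, and 18 months after the project starts (including a second summer". Under Recruitment of Sun Safety Advisors: "The project officers will collect the evaluation data at base-line before and after the first summer". Phase 1: data collection and analysis confirms the later two: "The second evaluation will be conducted after the first summer (mid-point of the study" and "The third workplace evaluation will be conducted 18 months after" the study's start.

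- **Outcomes** (Guiding frameworks): "The major outcomes for the evaluation are the changes in policy, procedures, and practices at the workplace level".
- **Content** (Phase 1: data collection and analysis): baseline covers "their current sun safety policy and practices", and a survey covers knowledge, attitudes and behaviors. For direct observation the article says "Site observations will record the use of sun safety practices" and names no evaluation. UV dosimetry is placed in the second summer.
- **Program** (The Sun Safety at Work implementation): the advisors lead the educational work during the first summer, which is the interval between baseline and the second evaluation.
- **Inference** (Recruitment of Sun Safety Advisors): comparing the baseline worker surveys with the second evaluation is said to yield measures of change attributable to the intervention.
- **Design** (Summary): the study is described as an uncontrolled before-after comparison across cases.

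**The concern.** Sun protection at work depends on the time of year, and the article says so itself under Occupational sun safety measures: "For Canada, this means UV protection should be used between April and August in many locations", with a March-to-October window elsewhere. Clothing, hat use, sunscreen use and awareness can plausibly move between a pre-summer and a post-summer evaluation with no program at all. Every workplace goes through the same sequence of baseline, summer with program, second evaluation, and nobody is observed through a summer without the program. The practice change therefore has two candidate causes that the data cannot separate, while the article names only one.

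This matters beyond phase 1. Phase 2: data collection and analysis bases the national resources on what phase 1 shows about how well particular sun safety initiatives work. A seasonal shift taken for a program effect would pass into that guidance.

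**Working it through.** There is no stated sample size, effect size or standard error to reproduce. The check sets the stated dates side by side and adds some calendar arithmetic.

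**1. What changes between baseline and the second evaluation.** Write the observed change in a practice measure as D = P + S, where P is the program's contribution and S is whatever would have happened over that summer anyway. A control group, or an earlier year without the program measured in the same way, would estimate S. The article has no control group and states no such earlier measurement. All 13 workplaces have the same order, so averaging over them does not remove S. D equals P only if S = 0, and nothing in the article supports that value. The error in reading D as P is exactly S, whatever the number of workers.

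**2. Which outcomes S touches.** Worker behavior and practice depend on weather and UV, and awareness perhaps does too. A written policy or procedure has little reason to appear or disappear with the season, so S should be near zero there.

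**3. Whether the 18-month evaluation supplies a season-matched comparison.** The article does not say which calendar month is month 0, so take both readings.
- *Month 0 near the baseline visit (assumption):* 18 = 12 + 6, so the third evaluation is 6 months out of phase with baseline. It falls in about the same season as the second evaluation, but data collection passes from the advisors to an independent researcher between those two.
- *Month 0 at a fall 2014 start* (Ethics approval expects completion in fall 2016 after two years): month 18 is about spring 2016. That is roughly baseline's season but before the second summer, which the evaluation is said to include. The assessor again differs from baseline.

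On neither reading does the article show a later evaluation that matches baseline by season and also fits its own description.

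**4. Whether the in-season measures help.** Dosimetry is done in the second summer, so no pre-program value exists to subtract. Site observations have no stated evaluation. If they too belong to the second summer, they have no baseline. If they are made at each evaluation, their first comparison contains S.

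**5. Calendar windows.** On the April-to-August window, a September or October second evaluation lies outside the protection season. On the March-to-October window it lies inside. The confounding in step 1 does not depend on which applies: before and after one summer are different seasons either way.

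**The case against.** The strongest reply has several parts.

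- **The survey may already ask about a summer.** No recall period is given, and a condensed article can leave that to the questionnaire. This stands. A reader might infer that neither of the first two evaluations catches peak sun exposure, but that is supported only for the dates of collection; a post-summer survey could ask about the summer just ended. The contrast would be repaired, however, only if baseline asked about the previous summer, and the article describes baseline as covering current practice.
- **Observations are not shown to occur at these evaluations.** This also stands. A reader might picture long sleeves worn for warmth in May or October being counted as sun protection. The article lists surveys and interviews before and after the first summer and does not place observations there, so that example and any percentage attached to it would be assumption.
- **The second evaluation may lie within the protection season.** This stands. The April-to-August example is Edmonton, which is in none of the four study provinces. Toronto, which is in one, has the March-to-October window. The article does not support saying that the second evaluation is wholly off-season.
- **Changing staff.** A reader might add that summer hires alter who is compared. The article does not mention such hires.
- **The design is openly uncontrolled, and this is a multiple case study.** The Summary admits limitations in general terms. It does not name season, and the causal sentence about the surveys remains. The cross-case comparison of more and less intensive programs could cancel a seasonal shift common to all workplaces, but workplaces choose their interventions and differ in province and industry. It also does not rescue the simple before-after attribution.

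**Conclusion.** The point holds for worker behavior and practice in the comparison of baseline with the second evaluation. By the article's own timing, season and program change together at every workplace without a control, so attributing that change to the intervention is not justified. It does not extend in any important degree to written policies and procedures, and it does not show that the before-after data are worthless: with a common summer reference period they would be considerably more informative.

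The size cannot be computed from the document. The bias equals the seasonal shift, which may be small, since spring and fall can resemble each other, and may have either sign. The conclusion rests on the stated order of the evaluations, the delivery of the program between them and the absence of a control. It does not rest on any assumed recall window, observation schedule or UV window. The statement about the 18-month evaluation depends on which month is month 0, and both readings are shown above.

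**What to change.** 1. **Survey wording.** Phrase the behavior items identically at every evaluation and refer them to working days in the most recent summer. Baseline then describes the pre-program summer and the later evaluations describe program summers. State the calendar month of the third evaluation: if it fell before the second summer, the items would ask about the first summer again.
2. **Site observations.** Record date, UV index and temperature at each one. Compare observed practice only between days with similar conditions, for example days with a UV index above 3, the threshold cited under Occupational sun safety measures.
3. **Wording of the inference.** Under Recruitment of Sun Safety Advisors, describe the practice result as a before-after change and name season as an alternative explanation.
4. **Measures without a baseline.** Report second-summer dosimetry, and any observations made only then, as descriptive.

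The cost is questionnaire wording, three extra fields on the observation form and a sentence of text. The real downside is unequal recall. With baseline in May and the second evaluation in October (assumed dates), the end of August lies about 9 months back at baseline and about 2 months back at the second evaluation. Workers not employed outdoors in the previous summer would have no baseline answer and should be counted. This recall difference should be reported as a limitation. It replaces a mismatch in the season being described with a mismatch in recall length, so the attribution should stay modest even after the change.
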